## Trial design

### Study objectives

The purpose of this study is to test the effectiveness and cost-effectiveness of a digital, app-based supported self-management (SSM) intervention for depression, adapted from a previously-tested [25] in-person SSM intervention. Specifically, we hypothesize that the digital intervention (VMood, which includes modified SSM) is superior to a control condition (the app delivering health information only) for reducing depression caseness among Vietnamese community-based adult populations screening positive for depression, and that the use of VMood will be cost-effective.

### Overall study design

The study will use a cluster stepped-wedge randomized controlled trial (RCT) design, with three stepped-wedges. Cluster stepped-wedge designs are pragmatic and appropriate for balancing scientific rigour with real world conditions, including the logistic and time constraints often faced by policy makers and health systems [29]. Stepped-wedge designs also represent an ethical approach in circumstances where access to evidence-based interventions is limited because they allow all participants to access the intervention as all clusters cross from the control into the intervention group [29].

In this study, randomization will occur at the commune level and communes will be assigned to receive either the VMood intervention or the control condition first. Participants in communes assigned to the control condition will be provided access to the VMood app and screening and assessment measures, but content will be limited to a video presenting general information about depression. In a typical stepped-wedge design, when a cluster crosses over from control to intervention, they remain in the intervention arm until the study is complete. In this case the intervention period will last three months in accordance with the VMood protocol. We will also collect follow-up data from each cluster three months after they have completed the intervention. Table 1 illustrates the timing of the intervention and control groups in the stepped-wedge design for one study district. Due to the size of the study, which will include 8 districts and 48 communes in total, all communes in the same district will begin the study at the same time but the entry of provinces will be staggered. The study has not started recruiting participants.

**Table 1 pone.0290328.t001:** VMood stepped wedge design by month—one district.

		1	2	3	4	5	6	7	8	9	10	11	12									
C1																						
C2																						
C3																						
C4																						
C5																						
C6																						
		Baseline																				
		Intervention																				
		Control																				
		Follow-up																				
	C	Commune																				

### Participants

#### Setting

The study will be carried out in eight Vietnamese provinces that represent diversity in terms of population composition, economic status and availability of mental health service resources. The study will take place in one district of each province, including six communes (municipal subdivisions) in each district for a total of 48 communes [see Table 2]. For logistical reasons, selected provinces represent a mix of provinces that previously participated in the in-person RCT and those that have not, though different districts and communes will be selected in all provinces that participated in the previous study to avoid bias.

**Table 2 pone.0290328.t002:** Participating provinces, districts, and communes.

Province	District	Communes
1	1	1, 2, 3, 4, 5, 6
2	2	1, 2, 3, 4, 5, 6
3	3	1, 2, 3, 4, 5, 6
4	4	1, 2, 3, 4, 5, 6
5	5	1, 2, 3, 4, 5, 6
6	6	1, 2, 3, 4, 5, 6
7	7	1, 2, 3, 4, 5, 6
8	8	1, 2, 3, 4, 5, 6

#### Inclusion and exclusion criteria

The trial will be implemented so that participants enter the study in a naturalistic manner. Community meetings will be organized to promote VMood, and all commune members will be invited to download the app, complete registration and informed consent and then complete the nine-item depression screening measure (Patient Health Questionnaire; PHQ-9 [30]). Healthcare staff members, funded by MOH, at the commune health stations and outpatient clinics will assist with publicizing the VMood app and encourage commune members to download it. Healthcare workers will be provided with information about the intervention as well as about the informed consent required to participate.

Inclusion criteria for the study are: 1) participant meeting depression caseness criteria based on the PHQ-9 measure (PHQ-9 score between 10–19) and 2) informed consent to participate in the study and complete all outcomes measures. Exclusion criteria include participants experiencing severe mental illness (PHQ-9 ≥ 20), including severe depression, suicidal ideation, or symptoms of other serious mental health conditions, who will be referred via an in-app notification to psychiatric and/or emergency care.

#### Informed consent

At registration, after downloading the VMood app, participants will be required to complete an online written informed consent form via the app in order to proceed to the contents of the app. All consent information collected through the app will be stored digitally. Participants needing support to complete the consent form or who have any questions will be provided with contact information for a member of the study team, who they can contact to complete the consent form either verbally (by phone) or by email (signed electronic copy).

### Interventions

#### Intervention condition

Supported self-management (SSM) is an evidence-based approach to the management of chronic disease which empowers the patient to participate in their own care by building appropriate skills with the support of a physician, lay provider, or other carer [31]. The in-person SSM for depression intervention that was previously tested [25] included a cognitive-behavioural therapy (CBT)-informed bibliotherapy intervention provided via the ASW [32] with supportive coaching provided face-to-face by non-specialist providers [33]. For the digital intervention used in this study, ASW was adapted to be delivered via the VMood smartphone app, with supportive coaching as needed provided through an online chat function by social workers. The VMood app maintains the core, skills-based components of the ASW, which include skill-building modules on behavioural activation, problem-solving, and realistic thinking. The ASW content will be delivered using multiple modalities, including text, video and audio recordings explaining the core concepts, and activities including quizzes and exercises that help participants to apply the skills to their own lives. Users will also be able to track their symptoms and monitor improvement with repeated PHQ-9/GAD-7 assessments at monthly intervals. VMood will also include features such as reminders and in-app notifications to promote engagement. As described above, the process of adapting the SSM intervention for app-based delivery and fidelity and usability testing will be reported elsewhere.

#### Control condition

The control condition will be enhanced treatment as usual. Depression is not widely recognized or treated in primary care in Vietnam and it is therefore likely that participants who meet the caseness criterion for depression based on PHQ-9 score will receive little or no treatment for depression. Enhanced treatment as usual will consist of access to the VMood app that has only the Introductory Modules turned on. These modules include the in-app screening measure (PHQ-9, with ongoing tracking) and the introductory video about depression, which describes symptoms and features of depression. Participants in the control condition will be informed that they are queuing for the intervention until they receive the intervention and, as described above, will receive access to the VMood introductory modules that provide information about depression and to the in-app screening measure (PHQ-9). The control VMood app will also include immediate referral to tertiary and/or emergency care for participants identified as having severe depression at screening (PHQ-9 ≥ 20) or who indicate they are experiencing suicidal ideation based on endorsing Question 9 on the PHQ-9. Participants in communes randomized to the control condition will be offered access to VMood’s full features, including the app-based SSM, following the period of control data collection as illustrated in Table 1.

### Outcomes

#### Primary outcome

The primary outcome of the study is depression caseness (PHQ-9 score ≥10 based on the Vietnamese version of the PHQ-9 [30] assessed at 3- and 6-months after initiation of the VMood intervention. The PHQ-9 and has been identified as the most suitable measures for use in a mobile app [16] and have been validated for use in Vietnam [30]. We will also collect demographic measures, including: age, sex, gender (if different from assigned sex at birth), education level, marital status, ethnicity, migrant status, employment status and classification, social insurance status and prior hospitalization due to mental illness.

#### Secondary outcomes

Secondary outcome measures will contribute to study findings across several categories, including clinical, quality of life, economic, and usability. Other clinical outcomes include changes in PHQ-9 and GAD-7 score from baseline to post-intervention. The effect of the intervention on quality of life, including dimensions such as social relationships, perceived well-being, and overall health [34], will be measured using the WHO Quality of Life- Brief (WHOQOL-BREF) [35]. Changes in use of alcohol and tobacco products during intervention use will be measured using the Fast Alcohol Screening Test (FAST) [36] and the Alcohol, Smoking and Substance Involvement Screening Test (ASSIST) [37] adapted to assess tobacco use only. We will also collect data on any other care for depression that participants in both the intervention and control group receive during the course of the study from the HEA.

For the cost-effectiveness analysis (details are presented below), we will estimate health-related quality of life using the EQ-5D-5L [38]. The EQ-5D-5L instrument is available in Vietnamese and has been validated in Vietnam, with country-specific weights based on social preferences obtained from a nationally representative sample available for the calculation of QALYs [39]. Costs attributable to health resource utilization will be estimated from self-reported inpatient and outpatient visits using the Health Economic Assessment (HEA) [40] adapted for the Vietnamese health system context. Indirect costs attributable to potential productivity gains will be measured using the validated Work Productivity and Activity Impairment Questionnaire: Depression (WPAID:D) [41,42].

Finally, the System Usability Scale (SUS) [43] will be used to assess the usability of the VMood app. Participants will complete the full suite of outcome measures at baseline (aside from the SUS), every three months until completing the intervention and at three months after completing the intervention (follow-up). The full suite of outcomes measures will be delivered online using REDCap electronic data capture tools hosted at the Institute of Population, Health and Development (PHAD) in Vietnam [44,45]. See Table 3 for a summary of the full suite of measures.

**Table 3 pone.0290328.t003:** Outcome measures.

Measure	Outcome	Frequency
** *Clinical Outcomes–Depression/Anxiety* **		
*PHQ-9	Depressive symptoms	Baseline, then monthly until 3 months post intervention
GAD-7	Anxiety symptoms	Baseline, then monthly until 3 months post intervention
** *Clinical Outcomes–Quality of Life* **		
WHOQOL-BREV	Functioning	Baseline, and at every 3 months until 3 months post-intervention
FAST	Alcohol use	Baseline, and at every 3 months until 3 months post-intervention
ASSIST–adapted	Tobacco use	Baseline, and at every 3 months until 3 months post-intervention
** *Economic Outcomes–Cost Effectiveness Analysis* **		
EQ-5D-5L	Functioning; can use this to calculate QALYs	Baseline, and at every 3 months until 3 months post-intervention
HEA–adapted	Costs attributable to health resource utilization	Baseline, and at every 3 months until 3 months post-intervention
WPAID:D	Indirect costs attributable to potential productivity gains	Baseline, and at every 3 months until 3 months post-intervention
** *Usability Outcome* **		
SUS	System (VMood) usability	At 3 months, then every 3 months until 3 months post-intervention

*Primary outcome will be depression caseness (binary outcome) at 3 months. Other clinical (depression) outcome will include PHQ-9 change scores.

#### Data collection

Participants will complete the full suite of outcome measures at baseline (aside from the SUS), every three months until completing the intervention and at three months after completing the intervention (follow-up). The full suite of outcomes measures will be delivered online using REDCap electronic data capture tools hosted at the Intitute of Population, Health and Development (PHAD) in Vietnam. Outcome measures will be disseminated using REDCap survey software [44,45] and will be completed by particpants at baseline and every three months, with a final assessment scheduled three months months after completion of the 3-month VMood intervention. See Fig 1 for full schedule.

**Fig 1 pone.0290328.g001:**
[figure not shown]
VMood schedule of enrolment, interventions, and assessments.

### Sample size and power calculation

The power calculation assumes that each commune would recruit an average of 8 participants and retain 7 participants after attrition and that the proportion of depression caseness (defined as PHQ-9 score between 10–19) in the control group is 42%, the same as in the previous study [25]. The calculation shows that for a type I error rate of 0.05, and an intracluster correlation coefficient (ICC) of 0.01 (based on data from the previous study on the binary outcome of having depression), a total of 336 participants recruited from 48 clusters (i.e., communes) have at least 80% power to detect treatment differences when the proportion of depression caseness in the intervention group is ≤ 30% (Table 4 below) [46]. The power calculation was performed using Stata 17 [46].

**Table 4 pone.0290328.t004:** Power analysis.

Proportion of depression caseness in Intervention Condition	Power
0.30	81%
0.31	74%
0.32	66%
0.33	57%
0.34	48%

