## Abstract

The COVID-19 pandemic has amplified mental health problems and highlighted inequitable gaps in care worldwide. In response there has been an explosion of digital interventions such as smartphone applications (“apps”) to extend care. The objective of this trial is to evaluate the effectiveness and cost-effectiveness of a digital depression intervention (*VMood*), delivered via a smartphone app. VMood is adapted from an in-person intervention that was delivered by non-specialist providers and shown to be effective in the Vietnamese context in our previous trial (2016–2019). A stepped-wedge, randomized controlled trial will be conducted across eight provinces in Vietnam. Adults aged 18 years and over will be recruited through community-based primary care centres and screened for depression using the embedded Patient Health Questionnaire-9 (primary outcome measure). Participants scoring 10–19, indicating depression caseness, will be randomly allocated to the intervention or control group until the target of 336 is reached. Secondary outcome measures will examine the effect of the intervention on commonly co-occuring anxiety, quality of life and work productivity, along with use of alcohol and tobacco products. Assessments will be administered through an online survey platform (REDCap) at baseline, and at every 3 months until 3 months post-intervention. Intervention-group participants will receive VMood for a 3-month period, with online support provided by social workers. Control-group participants will receive a limited version of the app until they cross into the intervention group. Generalized Linear Mixed-effect Models for clustered measures will be used for all outcomes data. We will conduct a cost-effectiveness analysis alongside the trial to capture VMood’s costs and benefits. This trial will provide evidence on the effectiveness and cost-effectiveness of a digital mental health intervention adapted from an in-person intervention. This trial will also contribute important information to the growing and promising field of digital mental health.

**Trail regulation.** Registered at ClinicalTrials.gov, identifier [NCT05783531].

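### The figure of 336 is the number expected after attrition (48 x 7), but the plan labels it as recruited and uses it as the allocation target; the recruitment figure its own assumptions imply is 384

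*Protocol article*

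**What the plan says.** Under *Sample size and power calculation*, the protocol article assumes that "each commune would recruit an average of 8 participants and retain 7 participants after attrition". It concludes that "a total of 336 participants recruited from 48 clusters (i.e., communes) have at least 80% power" to detect a fall in caseness to 30% or lower. Table 4 gives power of 81, 74, 66, 57 and 48% for intervention caseness of 0.30, 0.31, 0.32, 0.33 and 0.34.

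The abstract says that participants scoring 10 to 19 on the PHQ-9 "will be randomly allocated to the intervention or control group until the target of 336 is reached".

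No other total is given. In particular, 384 does not appear anywhere in the article.

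**The concern.** Eight recruited and seven retained in each of 48 communes make 384 and 336. The sample size paragraph therefore contradicts itself when it calls 336 the number recruited. The abstract carries the same figure into what reads as an enrolment target, and allocation comes before attrition. A team that worked to the published total would recruit an average of 7 per commune, with no allowance for the one-in-eight loss that the plan assumes.

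What is at stake is the claim of at least 80% power at 30% caseness. The margin is thin: Table 4 starts at 81% and is already 74% at 31%. The discussion also names attrition among participants waiting to cross over as a possible limitation, so the allowance matters.

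**Working it through.** **Inputs**

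- 48 communes; 8 recruited and 7 retained in each (*Sample size and power calculation*).
- Type I error: "for a type I error rate of 0.05". Two-sided is assumed here; the article does not say.
- Correlation: "an intracluster correlation coefficient (ICC) of 0.01".
- Control caseness: "in the control group is 42%, the same as in the previous study".
- Design: "cluster stepped-wedge randomized controlled trial (RCT) design, with three stepped-wedges", with communes assigned 1:1:1 (*Randomization and blinding*), so 16 communes per sequence.

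**Step 1: head counts**

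- Recruited: 48 x 8 = 384.
- Retained: 48 x 7 = 336.
- Attrition: 1/8 = 12.5%. Working back, 336 / (1 - 1/8) = 384.

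**Step 2: reproduce Table 4**

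The Hussey-Hughes variance of the treatment effect is

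Var = I s² (s² + T t²) / [(I U - W) s² + (U² + I T U - T W - I V) t²]

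where I is the number of communes, T the number of periods, s² the variance of a commune-period mean within communes, and t² the variance between communes.

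- Total variance: 0.42 x 0.58 = 0.2436. Hence t² = 0.01 x 0.2436 = 0.002436, and s² = 0.99 x 0.2436 / m for m participants per commune per period.
- Three periods, with one more sequence treated in each: I = 48, T = 3, U = 96, W = 16² + 32² + 48² = 3,584, V = 16 x (9 + 4 + 1) = 224.
- I U - W = 1,024, and U² + I T U - T W - I V = 9,216 + 13,824 - 10,752 - 10,752 = 1,536.

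With m = 7: s² = 0.034452. Var = 48 x 0.034452 x 0.041760 / (1,024 x 0.034452 + 1,536 x 0.002436) = 0.001770, so SE = 0.04207. Power at 30% = Φ(0.12 / 0.04207 - 1.96) = Φ(0.89) = 81.4%.

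| Participants per commune | 0.30 | 0.31 | 0.32 | 0.33 | 0.34 |
|---|---|---|---|---|---|
| Table 4 | 81 | 74 | 66 | 57 | 48 |
| m = 7 | 81.4 | 74.4 | 66.2 | 57.1 | 47.7 |
| m = 8 | 85.8 | 79.4 | 71.5 | 62.3 | 52.5 |
| m = 6.125 | 76.5 | 69.1 | 60.8 | 52.0 | 43.2 |

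All five entries match after rounding at m = 7, and none matches at m = 8. Adding a baseline period moves the m = 7 row by about 0.2 points (81.6% at 30%). A parallel-cluster formula with a design effect does not fit: it gives 61% at m = 7 and 66% at m = 8. Table 4 therefore rests on 7 per commune, and 336 is the number after attrition.

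**Step 3: what follows if enrolment stops at 336**

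336 x 7/8 = 294 retained, or 294 / 48 = 6.125 per commune.

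- *Loss applied in every period*, which is how the plan treats its own retained size: s² = 0.039374, SE = 0.04475, and power at 30% = Φ(0.12 / 0.04475 - 1.96) = Φ(0.72) = 76.5% (76.6% with a baseline period).
- *Loss building up in a straight line from 7 to 6.125 per commune*, with all available data used: 80.2% over three periods and 79.3% over four.

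**Step 4: what follows if 8 per commune are recruited**

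A flat retained size of 7 gives the stated 81.4%. A gradual fall from 8 to 7 gives about 84 to 85%.

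**The case against.** The strongest reply is that this is a labelling slip. The intended reading, 8 recruited and 7 retained, stands in the same paragraph, and sites that recruit 8 per commune will meet or exceed Table 4. That stands as far as it goes: power is lost only if 336 is applied as the enrolment figure. But 336 is the only total the article gives, it appears in two places as the number recruited or allocated, and one of the numbers has to change whichever was meant.

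Three stronger readings are tempting and are not supported.

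- *That power would certainly be 76.5%, with only 294 people analysable.* The analysis section says that the mixed model uses all available data, and assessments are scheduled every three months. Someone lost late still contributes earlier periods. So 294 is the number expected to complete, and 76.5% is the lower end of a range. The article does not give the timing of losses.
- *That allocation literally halts at the 336th participant.* The abstract's sentence is loose: the body randomises communes, after baseline assessment, and sets no stop at 336.
- *That early provinces could use up the places of later communes, because province entry is staggered.* Nothing describes a shared first-come quota. The plan is an average of 8 per commune, with six communes fixed in each of eight districts.

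It is also fair to say that the power formula is inferred. Sidedness, period structure and variance form were identified by matching Table 4. The match on all five values makes the choice credible but does not prove it.

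**Conclusion.** The inconsistency is real and can be seen from the head counts alone: 336 is the post-attrition number, described as recruited in the sample size section and used as the allocation target in the abstract. If it were followed as written, with the plan's own attrition, power for 42% versus 30% would be about 76.5 to 80% against the stated 81%, a shortfall of about 1 to 5 points. The lower end takes a flat retained size of 6.125 per commune; the upper end takes gradual loss with partial data used. Both assume a two-sided 0.05 test and the inferred Hussey-Hughes form.

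This should be corrected, but it is not a serious flaw. It does not affect the randomisation, the analysis model or bias, and it leaves Table 4 correct for 336 retained.

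**What to change.** In the abstract and in *Sample size and power calculation*, state 384 (an average of 8 in each of 48 communes) as the recruitment target and 336 as the number expected after attrition. Table 4 can then stay as it is. This asks for no enrolment beyond the 8 per commune already assumed, so the cost is two changes of wording. The article says that recruitment has not started, so the change can be made before enrolment.

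If recruitment really is to stop at 336, change the per-commune assumption to an average of 7 recruited and restate Table 4 for about 294 retained: about 76.5, 69, 61, 52 and 43% for 0.30 to 0.34. The claim of at least 80% power at 30% would then have to be withdrawn, or supported by a stated assumption about when participants are lost. In either case, one sentence naming the power method, the number of periods and the sidedness would let a reader check the table.
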